## **S1 Appendix. Study Protocol for Ethics Application**

### **EFFECT OF UPPER LIMB ISOMETRIC TRAINING ON HAMSTRING STRENGTH IN EARLY POSTOPERATIVE ANTERIOR CRUCIATE LIGAMENT RECONSTRUCTION PATIENTS: A RANDOMISED CONTROLLED TRIAL**

#### **Abstract**

This study aims to investigate the effects of upper limb isometric training (ULIT) combined with standard care of an anterior cruciate ligament reconstruction (ACLR) rehabilitation program on hamstring strength and physical function in the early-phase postoperative period. Early recovery of hamstring strength is critical for knee stability and functional rehabilitation post-ACL surgery. Hamstring strength deficits are prolonged issues in rehabilitation, with significant hamstring strength deficiencies in an early postoperative ACLR, especially using hamstring autograft, leading to functional limitations and an increased risk of secondary injuries. High knee muscle strength imbalances can hinder strength return in later stages. However, swelling, donor site pain, joint stiffness, and graft protection often neglect the direct activation of the hamstring in the early period. Also, clinical practice guidelines and consensus on early rehabilitation strategies are conflicting. While lower limb strengthening exercises are the mainstay of rehabilitation, this study explores the potential benefits of ULIT in promoting hamstring activation through the inter-limb posterior myofascial kinetic chain. This study hypothesise that participants receiving ULIT in addition to standard care will demonstrate better hamstring strength at 12 weeks post-operatively compared to those receiving standard care rehabilitation alone. A total of 32 patients who underwent ACLR with hamstring tendon autografts will be randomly assigned to either the ULIT group or a control group. The ULIT group performed upper limb isometric exercises in addition to standard postoperative rehabilitation, while the control group followed the standard rehabilitation protocol alone. We will measure hamstring and quadriceps strength using hand-held dynamometry at baseline (preoperative), 4, 8, and 12 weeks postoperatively. The primary outcome is the change in hamstring strength in the operated limb, while secondary outcomes included hamstring flexibility and patient-reported outcomes on symptoms, physical function and adherence. Statistical analysis will be conducted to compare the strength recovery between the two groups. It is believed that the results of this study will enhance knowledge about the global functional muscle concept, offer effective, safe, inexpensive, and feasible interventions, and promote further research on the interlimb connection of muscle activation and flexibility in heterologous muscle groups after ACLR.

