### **Data Collection**

The study will collect demographic data, as well as pre-, intra-, and postoperative data (see Table 3). Data will be gathered from the participants and their medical records for all the data collection forms (see Appendix A, C, and D). Baseline evaluations will be conducted throughout the pre-operative period, within a range of 14 days, to reduce any bias when selecting participants. The subsequent assessment in the 4th week ( $\pm 14$  days), 8 weeks ( $\pm 14$  days), and three months ( $\pm 14$  days) are scheduled at the Orthopaedic Clinic (van Melick et al., 2021). The blinded assessors will give all tests and questionnaires in person, ensuring participant consistency. These assessments will take place at four weeks, eight weeks and three months after the surgery. Phone consultations will be used for post-hospital discharge follow-up. Participants who cannot be reached by phone for a continuous period of 14 days starting from the assessment due date will be classified as lost to follow-up for outcome measurement.

intra-reliability had a value of 0.9269 [95% C.I.: 0.8909–0.9533] (Grgic et al., 2020; Karagiannopoulos et al., 2022; Romero-Franco et al., 2019).

The participants are directed to generate deliberate isometric contractions of their quadriceps or hamstring muscles, by pushing against the resistance provided by the dynamometer's arm with a perceived maximal effort of 100% (Grgic et al., 2020). During the formal testing, the participants conducted three maximum voluntary isometric contractions (MVIC) of knee extension lasting five seconds each for the quadriceps (Padulo et al., 2020). Similarly, This is followed by knee flexion testing for the hamstrings. A minute rest time will be given between the quadriceps and hamstring testing (Mellemkjær et al., 2024).

The assessor will consistently give instruction and verbal encouragement (see Appendix I). The participants are instructed to exert maximum force by either pushing with their quadriceps or pulling with their hamstrings against the dynamometer. The average and best scores of the peak forces will be recorded (Grgic et al., 2020).

The average scores of quadriceps and hamstring muscular strength during rehabilitation are quantified using the Quadriceps Index (QI) and Hamstring Index (HI), which are calculated using the formula:  $(\text{MVIC peak force of the affected limb} / \text{MVIC peak force of the unaffected limb}) \times 100$  (van Melick et al., 2021).

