## Sample Size

Sample size calculations are performed using SPSS version 29 for the primary outcome: differences between two means of Hamstring MVIC peak force symmetry index (see Figure 11). With the population standard deviation for the main outcome measure amount of 0.71 as in the Harput et al. study, type I error of 0.05, type II error of 0.2, 80% power, the minimum sample size required is 14 patients per group (28 in total). Expecting an attrition rate of 10%, 16 participants are considered for each study group.

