**Table 1 Hamstring and Quadriceps Muscle Strength Outcomes at 4, 8, and 12 Weeks, Mean  $\pm$  SD**

| Muscle                         | Limb       | Time Point       |                  |                  | P     |
|--------------------------------|------------|------------------|------------------|------------------|-------|
|                                |            | 4 wk             | 8 wk             | 12 wk            |       |
| Hamstring peak torque (Nm/kg)  | Involved   | 1.0 $\pm$ 0.5*   | 1.32 $\pm$ 0.9*  | 1.55 $\pm$ 0.8*  | <.001 |
|                                | Uninvolved | 1.86 $\pm$ 0.34† | 1.89 $\pm$ 0.46  | 2.05 $\pm$ 0.38† | .001  |
| Quadriceps peak torque (Nm/kg) | Involved   | 1.47 $\pm$ 0.62* | 2.18 $\pm$ 0.65* | 2.61 $\pm$ 0.67* | .001  |
|                                | Uninvolved | 2.60 $\pm$ 0.63* | 2.88 $\pm$ 0.73* | 3.14 $\pm$ 0.64* | .001  |

\*Quadriceps and hamstrings peak torques were significantly different between the 4th, 8th, and 12th weeks for the involved limb, and quadriceps peak torque was significantly different between the 4th, 8th, and 12th weeks for the uninvolved limb. †Significant difference for hamstrings peak torque between the 4th and 12th weeks for the uninvolved limb.

**Figure 11:** Sample size for the RCT based on the study by Harput (2015)

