## Statistical Analysis

The data analysis will be conducted using the SPSS Windows Version 29.0 software (SPSS, Chicago, IL, USA). The data will be summarised using descriptive statistics such as the mean and standard deviation, median and interquartile range, quantity and percentage, and frequency, depending on the distribution and type of data. This encompasses participant demographics as well as adherence to exercise. To evaluate the normality of the data, we will examine the skewness and kurtosis statistics (the ratio of the statistic to the standard error) by conducting the Shapiro-Wilk test. Boxplots are employed to detect outliers.

The main outcome measure, the mean changes in hamstring isometric peak force between 4 and 12 weeks, will be assessed using a paired t-test. The main hypothesis will be tested by comparing the changes in the mean difference between the intervention group and the standard

care group. The missing data will be analysed according to the intention-to-treat concept, considering the groups to which participants have been randomly allocated. Descriptive analysis, on the other hand, will describe missing data patterns in great detail to look for possible biases. If the data distribution exhibits non-normality or ceiling/floor effects, a non-parametric test (specifically, the Mann-Whitney test) will be conducted. Furthermore, this study will employ one-way repeated-measures ANOVA within-group measurements to investigate potential differences between the Quadriceps Index and Hamstring Index over an interval of time.

The secondary outcome data, which includes measurements of hamstring flexibility, range of motion, IKDC scores, and exercise adherence, will be summarised and evaluated in a manner consistent with the primary result. A repeated measures analysis of variance (ANOVA) will be used to examine the impact of rehabilitation and time on all the measured variables.

Statistical significance will be determined by a p-value of less than 0.05 (two-tailed) for all conducted tests with a 95% confidence interval.

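### The one-way repeated-measures ANOVA assigned to compare the Quadriceps and Hamstring Indices over time has one factor too few to answer that question

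*Protocol*

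**What the plan says.** After the primary comparison, the Statistical Analysis section of the protocol adds a supporting analysis: a "one-way repeated-measures ANOVA within-group measurements to investigate potential differences between the Quadriceps Index and Hamstring Index over an interval of time". It does not name the factor.

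Under Data Collection, average quadriceps and hamstring scores are "quantified using the Quadriceps Index (QI) and Hamstring Index (HI"), each defined as affected-limb over unaffected-limb peak force, times 100. Both indices therefore come from the same patient. The Abstract places strength testing by "hand-held dynamometry at baseline (preoperative), 4, 8, and 12 weeks postoperatively", so both are also repeated over time.

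The next paragraph of Statistical Analysis contains the only other analysis of variance: "A repeated measures analysis of variance (ANOVA) will be used to examine the impact of rehabilitation and time on all the measured variables". Its factors are treatment arm and time. It has no factor separating quadriceps from hamstring.

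**The concern.** A question about how two indices differ over time involves index and visit, both varying within the patient. A one-way repeated-measures ANOVA carries a single factor, so the test and the question do not match.

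The protocol expects strength to recover markedly between weeks 4 and 12. A test that responds to recovery can be significant whether or not the two muscles differ. Because the plan labels this test as the comparison of the two indices, a significant time effect could be written up as a quadriceps-hamstring difference that was never tested. Muscle imbalance around the knee is part of the protocol's background and problem statement, and no other planned analysis sets the two indices side by side.

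**Working it through.** The plan attaches no figure to this analysis, so there is none to reproduce. The check has two parts: what each one-factor reading tests, and how such a test behaves when the answer is known.

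**1. The possible one-factor readings**

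- Factor = time (the natural reading, given the within-group wording): the null is that one index has the same mean at every visit. The two indices are never compared.
- Factor = index, two levels: this is a paired t-test of QI against HI. Time is lost.
- Factor = all six index-by-visit cells (two indices, three postoperative visits): recovery alone can make the test significant.

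None isolates a difference between the indices over time.

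**2. Means**

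Table 1 in the Sample Size section gives peak torque by limb. Its hamstring row is "Hamstring peak torque (Nm/kg"). Involved over uninvolved mean, times 100, approximates each index (a ratio of means, not a mean of ratios):

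| | Week 4 | Week 8 | Week 12 |
|---|---|---|---|
| HI | 1.0/1.86 = 53.8 | 1.32/1.89 = 69.8 | 1.55/2.05 = 75.6 |
| QI | 1.47/2.60 = 56.5 | 2.18/2.88 = 75.7 | 2.61/3.14 = 83.1 |

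The week-12 values agree with the 76% (hamstring) and 82% (quadriceps) recovery cited in the Background.

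**3. Indices identical, both following 53.8, 69.8, 75.6**

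The protocol gives neither the SD of an index nor its correlation between visits. Assumed here: SD 15 to 30 points and correlation 0.3 to 0.7, equal across visits. Simulation used 3,000 runs per setting at two-sided 0.05, with 14 patients per arm (the calculated minimum) and 16 (the number planned). Proportion of runs in which the one-way time test is significant:

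| SD | n = 14 | n = 16 |
|---|---|---|
| 15 | 98-100% | 100% |
| 20 | 87-100% | 92-100% |
| 25 | 68-96% | 74-99% |
| 30 | 50-88% | 57-92% |

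The six-cell version rejected in 70% to 100% at n = 14. A two-factor analysis of the same data stayed near nominal: 4.5% to 5.9% for the index term and 4.2% to 5.9% for index by visit.

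**4. The same check with SDs approximated from Table 1**

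The delta method gives SD(HI) ≈ HI × √(CVi² + CVu² − 2r·CVi·CVu), where CVi and CVu are SD/mean for the involved and uninvolved limb and r is the between-limb correlation (not given; taken as 0 to 0.7). At week 4, CVi = 0.5/1.0 = 0.50 and CVu = 0.34/1.86 = 0.183. With r = 0, SD ≈ 53.8 × √(0.250 + 0.033) ≈ 29; with r = 0.7, SD ≈ 53.8 × √(0.283 − 0.128) ≈ 21. The ranges are about 21-29, 38-51 and 31-42 points at weeks 4, 8 and 12.

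With these SDs, n = 14 and correlation between visits 0.3 to 0.7, the time test is significant in about 30% to 82% of runs, and in 38% to 64% at correlation 0.5. A Greenhouse-Geisser correction lowers the figures somewhat (24% to 77% overall).

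**5. The converse: indices constant at 70 and 80**

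The indices now differ by 10 points at every visit and neither changes. Under the assumptions of step 3, the one-way time test rejects in 4.3% to 5.3% of runs. It does not respond to a real, constant difference.

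**The case against.** The strongest defence is that the sentence is loosely worded and the test is sound. Table 1 examines each muscle separately across weeks 4, 8 and 12, and the authors may have meant the same for each index. A one-way test over time would then be correct, and only the stated purpose would be wrong. This is plausible, but the sentence still needs correcting.

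A reader might infer from the simulation that the test has a false-positive rate many times 5%, or that it will be significant in nearly every trial. Neither is supported. In steps 3 and 4 the means do change over time, so rejecting the time null is correct: those percentages are power to detect recovery. They mislead only if a time effect is reported as a difference between indices, and the protocol does not say it will be. With SDs taken from the protocol's own table, the rate can fall to about 30%.

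A reader might also infer that the plan fails to test whether upper limb training alters quadriceps-hamstring balance. The objectives and hypotheses never ask that. They concern hamstring strength, IKDC score, flexibility and adherence, and the later ANOVA on arm and time covers between-arm effects on each measured variable. These points limit the importance of the finding, but they do not supply the missing factor.

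**Conclusion.** The mismatch is real and rests on the wording alone: under no one-factor reading does the named test answer its stated question, and nothing else in the protocol compares the two indices. The simulated rates show only how easily the result could be misread. They depend on index SDs and correlations that the protocol does not give, on equating the indices with ratios of Table 1 means, and on using only the three postoperative visits that Table 1 covers.

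The consequence is limited. Comparing the indices is not a listed objective, and the primary between-arm comparison of hamstring strength does not depend on it. This is a minor correction to a supporting analysis.

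**What to change.** Choose one of two wordings.

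- **If a comparison of the indices is wanted:** replace the one-way test with a within-patient model with factors index (QI, HI) and visit. Equivalently, form D = QI − HI for each patient at each visit and run repeated measures on D: the mean of D against zero gives the index term, and the change in D across visits gives index by visit. Label it exploratory, since 14 to 16 patients per arm will estimate these terms imprecisely. Arm may be added as an optional exploratory between-patient factor.
- **If only recovery was meant:** restate the aim as change over time in each index within an arm, and say that the result supports no comparison of muscles or of arms.

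Either way, name the factor or factors. The cost is one sentence; the data and software stay the same.

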## **Specific Objectives**

1. To investigate the difference in hamstring strength between the ULIT and the standard care group compared to the standard care alone group at 4, 8, and 12 weeks post-ACLR.
2. To measure the changes in physical function based on the IKDC score in the ULIT group compared to the standard care group at preoperative and 12 weeks post-ACLR.
3. To evaluate the effect of ULIT on hamstring flexibility, measured by the active knee extension test (AKET) test, compared to standard care alone at preoperative and 12 weeks post-ACLR.
4. To analyse the relationship between patient adherence to ULIT and improvements in hamstring strength and physical function over the 12-week rehabilitation period.

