### **Intervention Group (ULIT + Standard Care)**

A single physiotherapist will administer the ULIT. The treating physiotherapist will present the ULIT to patients in verbal, demonstration, and written formats. In the fourth week following ACLR surgery, the treating physiotherapist will conduct the ULIT as a single, personalised session. The treating physiotherapist will instruct patients to follow the ULIT from 4 to 12 weeks post-operatively together with the standard care ACLR rehabilitation protocol. The ULIT comprised three concise isometric exercises: 1) wall push-up, 2) shoulder extension, and 3) shoulder external rotation (see Appendix I). The intervention group will be instructed to continue the ULIT plus standard care rehabilitation daily as a warm-up and home exercise programme for eight weeks.

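### The assessment visits and the analysis window for IKDC and hamstring flexibility are not fixed, and a change score from a pre-surgical value may be an inefficient way to compare the arms

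*Protocol*

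**What the plan says.** Four parts of the protocol bear on when IKDC and AKET are measured and how they are compared.

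- **Specific Objectives.** Objective 2 takes IKDC in the ULIT group "compared to the standard care group at preoperative and 12 weeks post-ACLR". Objective 3 takes AKET "compared to standard care alone at preoperative and 12 weeks post-ACLR". Objective 1, on strength, names weeks 4, 8 and 12 instead.
- **Data Collection.** "Baseline evaluations will be conducted throughout the pre-operative period, within a range of 14 days". For follow-up, "The blinded assessors will give all tests and questionnaires in person", and the next sentence adds: "These assessments will take place at four weeks, eight weeks and three months after the surgery".
- **Secondary/Explorative Outcomes.** Both instruments are described, without timing.
- **Statistical Analysis.** The primary outcome is "the mean changes in hamstring isometric peak force between 4 and 12 weeks", examined with a paired t-test and then by comparing the mean changes between arms. Flexibility and IKDC, with range of motion and adherence, "will be summarised and evaluated in a manner consistent with the primary result". A repeated-measures ANOVA is also planned for every measured variable. No visits are named for the secondary outcomes.

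The Intervention Group section has the physiotherapist "instruct patients to follow the ULIT from 4 to 12 weeks post-operatively".

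**The concern.** An assessor at the week-4 or week-8 visit cannot tell from the text whether IKDC and AKET are due. The analyst cannot tell whether carrying over the primary method means the same window (week 4 to week 12) or only the same kind of summary and test. These choices yield different endpoints. One starts before the operation and the other starts around the time ULIT begins, and the two need not agree. A later analysis plan can choose between windows, but it cannot recover week-4 data that were never collected.

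Physical function is named in the main objective and flexibility is a secondary objective, so it should be settled in advance which contrast represents each.

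There is also a question of efficiency. The primary method compares mean changes. Applied from a pre-operative start, it subtracts a value measured on a knee that has not yet been operated on or had its tendon harvested. How well that value predicts week 12 is unknown. If it predicts poorly, subtracting it adds noise.

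**Working it through.** **Step 1: which contrasts exist under each schedule**

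| Schedule followed | Visits for IKDC and AKET | Pre-op to week 12 | Week 4 to week 12 | Levels of time in the ANOVA |
|---|---|---|---|---|
| Specific Objectives | pre-op, 12 | yes | no | 2 |
| Data Collection, read as covering all instruments | pre-op, 4, 8, 12 | yes | yes | up to 4 |

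The pre-operative-to-12-week contrast is available in both rows. The week-4-to-week-12 contrast exists only in the second.

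**Step 2: is the pre-operative-to-12-week comparison biased?** Study Design and Randomisation and Allocation both place allocation after baseline testing. Both arms then have the same type of surgery and standard care over the same period. Surgery, harvest and the first four weeks therefore contribute to both arms, and the randomised difference between arms is unbiased.

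**Step 3: precision of a change score against adjustment.** The protocol states no variance or correlation for IKDC or AKET, so the correlation r between the pre-operative and 12-week values is an assumption, shown over a range. Equal standard deviations at the two visits are also assumed. Relative to the variance of an unadjusted 12-week comparison, set to 1:

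- change score: 2(1 − r)
- ANCOVA on the pre-operative value: 1 − r²
- ratio: 2(1 − r)/(1 − r²) = 2/(1 + r)

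| Assumed r | Change score | ANCOVA | Ratio |
|---|---|---|---|
| 0.1 | 2 × 0.9 = 1.80 | 1 − 0.01 = 0.99 | 1.82 |
| 0.3 | 2 × 0.7 = 1.40 | 1 − 0.09 = 0.91 | 1.54 |
| 0.5 | 2 × 0.5 = 1.00 | 1 − 0.25 = 0.75 | 1.33 |
| 0.7 | 2 × 0.3 = 0.60 | 1 − 0.49 = 0.51 | 1.18 |

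Below r = 0.5 the change score is less precise than ignoring the baseline altogether. At r = 0.3, 14 patients per arm analysed by change carry about the information of 14 × 0.91/1.40 = 9.1 per arm analysed by ANCOVA.

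These are large-sample formulas. Estimating the slope costs one degree of freedom: with 14 per arm, 28 − 3 = 25 instead of 28 − 2 = 26.

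The planned ANOVA does not avoid the issue. With two time points, its group-by-time term is the same test as the comparison of change scores.

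The protocol's sample size (14 per group, 16 after attrition) concerns hamstring strength. It is used here only to illustrate scale.

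**The case against.** The strongest reply is that nothing is broken.

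- The objectives state the time points for both outcomes, and a specific statement should govern a general one.
- The cross-reference to the primary analysis most naturally means the same type of summary, test and fallback. It also covers exercise adherence, for which a week-4-to-week-12 difference makes little sense.
- In Data Collection, the sentence about giving tests in person concerns mode of administration. Adherence monitoring schedules the kinesiophobia scale only pre-operatively and at 3 months, so the protocol does confine some instruments to those visits.
- The objectives do not say *only*, so measuring at every visit would satisfy both sections.
- Data Collection points to a Table 3 that is not visible in the available text and may hold a visit schedule.

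Most of this stands, and it limits the point to one of clarity and efficiency. It does not remove it. The two sections can still be read differently, Statistical Analysis names no window, and even the charitable reading leads to a comparison of changes from a pre-surgical value.

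A reader might go further and infer that these endpoints cannot be computed. Step 1 shows that they can. A reader might also infer that a pre-operative-to-12-week change says nothing about ULIT, because 4 of the 12 post-operative weeks (33%) and the operation precede it. That applies to a within-group change, not to the randomised comparison. The 33% is a share of the calendar and measures neither bias nor precision. No figure in the protocol shows that surgical variation dominates.

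**Conclusion.** The point holds in a limited form. The visits for IKDC and AKET can be read in two ways, and the window for their analysis is left open. The contrast named in the objectives is computable under either reading, and its between-arm comparison is unbiased.

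The cost of comparing simple changes is a loss of precision that depends on an unknown correlation. Over assumed values from 0.1 to 0.7, the variance is 1.82 to 1.18 times that of ANCOVA, and 1.54 times at r = 0.3. This rests on equal standard deviations at the two visits and on large-sample formulas. If the correlation is high, little is lost. Only secondary outcomes are affected, but the remedy is nearly free and closes the choice of window before data are seen.

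**What to change.** 1. Reconcile Specific Objectives and Data Collection by stating, for IKDC and AKET separately, the visits at which each is taken.
2. In Statistical Analysis, replace the cross-reference to the primary method for these two outcomes with a named endpoint: the between-arm difference in the 12-week value, adjusted for the pre-operative value by ANCOVA, with its 95% confidence interval. This uses values collected under either schedule.
3. State that any week-4 or week-8 values are descriptive only. A week-4 value is measured after allocation, and with the visit window of ±14 days it may fall after ULIT has begun, so it is not a clean baseline.

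Adding week-4 measurements is optional, and the endpoint does not need them. The cost is a wording amendment and one degree of freedom in each analysis. No extra visit, staff or patients are required.
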